# Retention in physically demanding jobs of individuals with low back pain: study protocol for a randomised controlled trial

**DOI:** 10.1186/s13063-015-0684-3

**Published:** 2015-04-16

**Keywords:** Low back pain, Sick leave, Workplace intervention, MRI, Weight-bearing, Occupational medicine, Physically demanding jobs, G-MRI

## Abstract

**Background:**

Low back pain is prevalent and is a frequent cause of disability and sick leave among working adults. Individuals with low back pain often consult general practice or other health care providers which often results in a unilateral intervention focussed on their symptoms. Employment is associated with physical and mental well-being, so, patients may benefit from an early additional occupational medicine intervention. For individuals with physically demanding jobs it can be especially challenging to retain their jobs. The aim of the ‘GoBack trial' is to develop and evaluate the efficacy and feasibility of an occupational medicine intervention for individuals with low back pain in physically demanding jobs.

**Methods/design:**

We will conduct a randomised controlled trial enrolling 300 participants with difficulty in maintaining physically demanding jobs due to low back pain for a current period of 2 to 4 weeks. Participants will be randomised and stratified according to their age and gender before being allocated in a 1:1 ratio to either control or additional occupational medicine intervention. Both groups will receive conventional treatment for their low back pain during the study. All participants will be thoroughly assessed for causes of low back pain and potential prognostic factors by questionnaires, clinical specialist assessments and magnetic resonance imaging (MRI) scans of the lumbar spine. Primary outcome is the accumulated duration of self-assessed sick leave (in days) due to low back pain during 6 months from baseline. Secondary outcomes include general self-rated back pain, disability and screening for potential prognostic factors: fear avoidance behaviour, disability, health status and degenerative MRI findings. For tertiary purposes selected outcomes will also be assessed after 1 and 2 years from baseline.

**Discussion:**

Many guidelines exist for the management of low back pain, but they provide limited guidance on occupational aspects. The findings from this randomised trial will provide high-quality evidence for the efficacy and feasibility of an occupational medicine intervention model for individuals with low back pain in physically demanding jobs.

**Trial registration:**

This trial was registered with ClinicalTrials.gov (identifier: NCT02015572) on 29 November 2013.

## Background

Low back pain (LBP) is a recognised public health problem, and the lifetime prevalence may be up to 80% in industrialised countries [1]. LBP is a common reason for doctor visits and is a significant cause of sick leave and disability pension with huge personal and socio-economic consequences [2]. Despite increased attempts of prevention, the incidence curves of LBP have still not been altered. The explanation is supposed to be that LBP and the resulting function deterioration are a complex combination of physiological, psychological, cultural and social factors. It is therefore recommended to focus on tertiary prevention in patients who have already developed LBP [3]. Medical treatment may reduce the physical and mental discomfort, while it has not been able to improve the possibilities for return to work [4]. Further, it has been demonstrated that over 60% of LBP patients from general practice may experience more than three episodes of pain after their first episode [5]. Twin studies indicate that disc degeneration and LBP correlate more closely with genetic heritability than with physical load [6,7]. Despite a large heterogeneity in LBP conditions, the overall picture is clearly that LBP is not a self-limiting condition [5,8,9]; therefore, return to work or work retention seems to be a good outcome measurement for LBP interventions.

Even with the multitude of different treatments offered to patients with LBP, there is no treatment that has been proven to be highly effective. In recent years focus has therefore been on cognitive behavioural therapy and the attachment to the labour market [10,11]. Occupational attachment is associated with physical and mental well-being [12], and there seems to be negative association between long-term sick leave and later labour market attachment [13]. Although there is little knowledge about prognostic factors, it seems that job satisfaction and opportunity to work adaptation are important factors for work rehabilitation [14]. Furthermore, early intervention including contact with the individual who is ill with LBP, workplace visits and effective cooperation between the individual, the employer and the clinical team may prevent permanent exclusion from the labour market [15]. From workplace and municipal intervention programs we know that occupational medicine intervention has an effect on work rehabilitation, albeit a small one [16]. The literature in this field is confusing due to considerable variations of the definitions of both LBP as well as recovery [17,18].

Fear avoidance behaviour has been shown to be an essential element of the disabling pathway in chronic LBP, and biopsychosocial models have been an established part of most interventions [19,20], but there is limited knowledge about the effect on occupational rehabilitation. Physical exercise alone has only limited influence on the work ability of LBP patients, whereas supervised training and a behavioural therapeutic approach seem to be much more effective in reducing sick leave [21]. Therefore, intervention for individuals on sick leave with physically demanding jobs should be based on cognitive behaviour treatment addressing fear avoidance behaviour towards the workplace, and job modifications in combination with supervised physical exercise.

The objective of this study is to evaluate whether an additional occupational medicine intervention with focus on early workplace oriented counselling and workplace intervention can retain individuals with physically demanding jobs and LBP in employment. The secondary aims are to identify prognostic factors for success of this occupational medicine intervention using the baseline outcomes: pain level, health status, fear avoidance behaviours, job satisfaction, work ability, and degenerative magnetic resonance imaging (MRI) findings. Among these variables, we aim to identify individuals who already have a good prognosis and therefore have no need for this larger scale intervention. Later, a cost-benefit analysis of the intervention will be performed.

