### Sample size

For a two-sample pooled *t*-test of a normal mean difference with a two-sided significance level of 0.05 (*P* < 0.05), assuming a common standard deviation of 17 days [17,34], a sample size of 127 participants per group is required to obtain a power of at least 80% to detect a mean difference of 6 days. Expecting some drop-outs during the trial period (less than 20%), it was decided for pragmatic reasons to enrol 300 participants in total (that is, 150 participants in each group). Including 300 participants in the intention-to-treat population, based on the assumptions above, corresponds to a statistical power of 86.1% to detect a mean difference of 6 days.

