### Statistics

Data analyses will be performed using the SAS System for Windows (Release 9.3, SAS Institute Inc., Cary, NC, USA). Descriptive statistics of participant baseline characteristics will be presented for both groups to assess their comparability. Continuous data will be analysed using an Analysis of Covariance (ANCOVA), with a factor for Group, using the baseline value as a covariate to reduce the random variation and increase the statistical power. Unless stated otherwise, results will be expressed as the difference between the group means with 95% confidence intervals (CIs) based on a General Linear Model (GLM) procedure. *P*-values will only be reported if appropriate. We will attempt to follow up all randomised participants, even if they withdraw from allocated treatment. The main analyses will be on sick leave after 6 months where participants will be analysed according to the allocated group. The Cox proportional hazard model will be used to analyse differences in time until return to work, including the intervention group as the only independent variable.

The cost-effectiveness analysis of our occupational medicine intervention will include predictors of return to work, based on questionnaire outcomes, the MRI evaluation and clinical examination. This study is testing an additional intervention to the treatment provided by the participants’ GP; therefore, the direct intervention costs included the costs of the workplace and our occupational medicine intervention. This will be compared to the costs of production losses estimated by a price of production loss of a worker per day. Further direct non-health care costs will be included (such as pension expenses, loss of productivity, schooling and redeployment).

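### The secondary aim infers no need for the intervention from a good prognosis, but that depends on the between-arm difference in those people, and no group-by-factor comparison is stated

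*Protocol article*

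**What the plan says.** The last paragraph of the Background gives the secondary aims. The first is to "identify prognostic factors for success of this occupational medicine intervention", using six baseline variables: pain level, health status, fear avoidance, job satisfaction, work ability and degenerative MRI findings. The next sentence draws a consequence: "Among these variables, we aim to identify individuals who already have a good prognosis and therefore have no need for this larger scale intervention".

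The Statistics section describes three analyses that bear on this:
- Continuous outcomes: an ANCOVA "with a factor for Group, using the baseline value as a covariate to reduce the random variation and increase the statistical power".
- Time until return to work: a Cox model "including the intervention group as the only independent variable".
- Predictors, mentioned only here: "The cost-effectiveness analysis of our occupational medicine intervention will include predictors of return to work, based on questionnaire outcomes, the MRI evaluation and clinical examination".

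None of these is stated to compare the group difference between levels of a baseline factor. The Sample size section covers the overall difference in sick-leave days only.

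**The concern.** The word *therefore* carries the problem. A baseline factor can predict few sick-leave days in both arms while the gain from the intervention stays the same. Such a factor is prognostic, but it does not show that the intervention is unnecessary. The phrase about success has the same weakness: a participant in the intervention arm who does well may have recovered without it. Both statements concern how the between-arm difference behaves at different levels of the factor.

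What is at stake is targeting. The Discussion says that positive and cost-effective results could change policy. If the Background's inference were followed, a subgroup could be described as not needing the intervention without a comparison of the arms within it. A marker of natural recovery could likewise be reported as a predictor of intervention success.

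**Working it through.** **Logic.** Write sick-leave days as a + b·Group + c·Factor + d·(Group × Factor). Prognosis is c. The benefit at a given level of the factor is b + d·Factor. A large c says nothing about d, so knowing c alone cannot identify who has little to gain.

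**Inputs (Sample size section).** The design is a "two-sample pooled *t*-test of a normal mean difference with a two-sided significance level of 0.05", "assuming a common standard deviation of 17 days", with a 6-day difference, at least 80% power, 127 per group required, 300 enrolled (150 per group) and drop-out below 20%.

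**The plan's own figures.** The normal formula gives n = 2 × (1.960 + 0.842)² × 17² / 6² = 127 per group. The t-test solution is 126.99. With 150 per group, t-test power is 86.1%. Both stated figures reproduce, and both concern the overall difference.

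**Precision for a difference between subgroups.** Let n be the number per arm and p the good-prognosis share. The documents give no p, so 0.25 to 0.50 is assumed.
- SE of the overall effect = 17 × √(2/150) = 1.96 days.
- SE of the interaction = 17 × √(2/(np) + 2/(n(1−p))).
- Power ≈ Φ(δ/SE − 1.96), plus a negligible opposite tail. The interaction detectable with 80% power = 2.80 × SE.

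| n per arm | p | SE (days) | Power, 6-day interaction | Detectable at 80% | 95% CI half-width, good-prognosis subgroup |
|---|---|---|---|---|---|
| 150 | 0.50 | 3.93 | 33% | 11.0 | 5.4 |
| 150 | 0.30 | 4.28 | 29% | 12.0 | 7.0 |
| 150 | 0.25 | 4.53 | 26% | 12.7 | 7.7 |
| 120 | 0.50 | 4.39 | 28% | 12.3 | 6.1 |
| 120 | 0.30 | 4.79 | 24% | 13.4 | 7.9 |
| 120 | 0.25 | 5.07 | 22% | 14.2 | 8.6 |

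The 120-per-arm rows apply 20% drop-out to 150. The last column is 1.96 × 17 × √(2/(np)).

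**Reading.** At p = 0.50 the interaction SE is twice that of the overall effect. For 80% power to detect a 6-day interaction, about 1,010 analysed participants would be needed at p = 0.50, or 1,202 at p = 0.30. A larger interaction is easier to see. If the overall effect were 6 days and a good-prognosis half gained nothing, the other half would gain 6/0.5 = 12 days, and power would be 86% with 150 per arm. Within the good-prognosis subgroup, a half-width of 5.4 to 7.7 days (150 per arm) is close to or above the 6-day design effect. A null result there would therefore be weak support for a lack of need.

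**The case against.** **Unseen documents.** This is a journal article, and an analysis plan or fuller protocol may specify how the prognostic aim is modelled. The ANCOVA and the Cox model are described as between-group analyses and are not assigned to this aim. This stands. The absence of an interaction model is not itself the fault. The point rests on the inference the Background states, which a more detailed plan would not correct.

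**The models.** A reader might infer that the planned models contain only the group effect. The article does not support that. Only the Cox model is group-only. The ANCOVA also has the baseline value, and predictors of return to work enter the cost-effectiveness analysis. What can be said is that no group-by-factor comparison is stated.

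**The zero floor.** Sick-leave days cannot fall below zero, so someone expected to have very few under usual care has little to gain in days, whatever the relative effect. This gives the inference partial validity. It would need prognosis estimated under control care and a stated threshold, and the Background gives neither. It would also leave pain and disability, which are secondary outcomes, untouched.

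**Consequences.** A reader might also infer that the trial will withhold the intervention from a subgroup, or will ignore the control arm in the prognostic work. The article commits to neither.

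**Size.** The power figures show how little a sound analysis could establish. They do not measure how wrong the stated inference would be. This also stands, and it is why the aim should be labelled exploratory.

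**Conclusion.** The point holds as a wrongly stated inference with a cheap remedy. A good prognosis alone does not show that the intervention is unnecessary, and a predictor of outcome is not by itself a factor for the intervention's success. Both depend on the between-arm difference at levels of the factor, and the article states no such comparison.

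On size, a sound analysis of this aim would have about 26–33% power for a 6-day interaction with 150 per arm, and 22–28% with 120. These figures assume an SD of 17 days in every subgroup, a two-level factor with a 25–50% good-prognosis share, a normal approximation, and no precision gained from the baseline covariate. Six factors are listed, so chance findings are a further reason for caution. The low power is not a defect of the sample size, which was set for the overall comparison. That comparison and the primary analysis are unaffected.

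**What to change.** 1. Reword the aim in the Background so that a lack of need rests on a small estimated between-arm difference, not on good prognosis alone. Describe factors that predict outcome regardless of arm as prognostic only.
2. For each listed baseline factor, add the factor and a Group × factor term to the 6-month sick-leave model. Report the between-arm difference in days at levels of the factor, with 95% CIs.
3. Analyse the MRI factor in those scanned. State that the scan follows allocation (within 2 weeks) and that participants may be excluded after it, so this set may not be everyone randomised.
4. Label all of this exploratory.

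The cost is a change of wording and a few extra models on data already to be collected. The downside is a more modest claim, because the intervals will be wide and most factors will probably not support a firm statement either way.

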## Methods/design

As illustrated in Figure 1, this is a randomised controlled trial with 1:1 allocation. It is conducted in accordance with the SPIRIT (Standard Protocol Items: Recommendations for Interventional Trials) 2013 guidelines [22]. The study is designed to investigate if an additional occupational medicine intervention can retain individuals with physically demanding jobs and LBP in gainful employment over a 6-month period. Eligible participants will be randomised after baseline measurements to one of two parallel groups: 1) control, 2) additional occupational medicine intervention. Data are collected at each stage of the trial, at initial telephone screening, allocation, occupational sessions and through all follow-up visits, and are reported according to CONSORT (Consolidated Standards of Reporting Trials) statements [23]. The study is approved by the Local Research Ethics Committee, Region H, Denmark (H-3-2013-161) 20 November 2013.

**Figure 1 Fig1:**
[figure not shown]
Participants flow through the study.

### Inclusion criteria

Eligible participants are persons between 18 and 65 years of age with a current episode of 2 to 4 weeks of LBP with a self-reported physically demanding job, who independently of sick leave status, express concerns about the ability to maintain their current job. They must be able to speak, read and understand Danish in such a way that they can give informed consent for participating. The potential participants have to be in employment for at last 30 hours/week and must accept workplace visits by an occupational physician (OP) or physiotherapist. According to Robreok *et al*. [24], physically demanding work is defined by a self-reported patient statement using a single question: *Would you strongly agree, agree, disagree or strongly disagree that your work is physically demanding?* Those individuals who strongly agree or agree are considered to have physically demanding work. LBP is defined as pain located in the lower back with or without radiating symptoms and must fulfil International Classification of Diseases, 10th Revision (ICD-10) back pain codes: DM43.1; DM47; DM48.0; DM54.3-54.9; DM 51.1; DM51.2; DM51.3; DM 51.9; DM53.8; DM53.9. [http://apps.who.int/classifications/icd10/browse/2010/en].

### Exclusion criteria

The exclusion criteria are pregnancy, severe somatic or psychiatric disease, cancer or metastatic disease, severe co-morbidity, treatment or referral to outside providers (for example, surgery) or contraindications for having a conventional MRI.

### Study settings and recruitment

Participants are recruited in the capital region of Copenhagen (Denmark) and the surrounding counties (Region H) with approximately 1.7 million residents. Physicians, health providers and general practitioners (GPs) will continuously be informed of the possibilities of referral to the project. The referrer may suggest participation to any patient with a current episode of 2 to 4 weeks of LBP and self-reported physically demanding work. Potential eligible patients will be referred to the Department of Occupational and Environmental Medicine, Copenhagen University Hospital, Bispebjerg and Frederiksberg, which will contact the candidate by telephone and screen for criteria of inclusion and exclusion. If needed, recruitment via advertisement can be an option. Individuals who fulfil the inclusion criteria are forwarded written information of the study and are scheduled within one week for the baseline visit at The Parker Institute, Department of Rheumatology, Copenhagen University Hospital, Bispebjerg and Frederiksberg.

Qualified physicians from the Parker Institute, Department of Rheumatology, will conduct all baseline and follow-up health assessments. They are not allowed to treat the participants or take action in the occupational medicine intervention but will take action if the physical examination reveals conditions which need further clinical intervention. Outcomes will be recorded in dedicated databases at baseline, half-a-year (primary endpoint), and at the one-year follow-up at The Parker Institute, Department of Rheumatology. The GPs are continually informed of the allocation and occupational medicine intervention plan. In addition, imaging data and subsequent interpretation are automatically stored on dedicated imaging servers within the capital region of Denmark (Region H) for 10 years as part of normal clinical practice. The 2-year follow-up is a structured interview conducted by independent non-treating personnel from the occupational department.

### Study timeline

The primary health provider (for example, the GP) can provide a letter of introduction, contact information and informed consent. Both the primary health provider and participants can find these documents and additional information on the trial’s dedicated website www.goback.dk (in Danish). The screening telephone interview by the occupational department’s staff takes about 10 to 15 minutes, and eligible participants are mailed the baseline visit schedule and the manual Guidance for Participants in Clinical Studies.

The enrolled participants meet at The Parker Institute, Department of Rheumatology, for baseline visit within a week after the screening interview. The institute’s staff reviews the informed consent document with the participant before signing. The participants complete the baseline questionnaires on a validated touch screen [25] with information including demographic and personal data, general health information, history of work-related factors, sickness absence, LBP pain score, fear avoidance and back-specific disability. A qualified physician then performs a clinical examination and reviews relevant health-related answers, noting if further information or examinations are necessary or there is a need for further referral. The physician completes the hospital’s web-based (OPUS) clinical report that includes systematic questions on key eligibility criteria, clinical findings, red flag conditions and a LBP-focussed case summary. This report is sent to the participant’s GP. When questionnaires and clinical examinations have been obtained, the randomisation takes place and the group allocations are revealed to the participants. The participants in the intervention group will have their first occupational medicine intervention session the same day.

Due to logistics, the participants will be scanned at baseline as a post-allocation examination within 2 weeks. As part of the one-year follow-up all participants will be rescanned in the same setting and by the same MRI protocol. The MRI scans take place at the Department of Radiology, Frederiksberg Hospital, and a 0.25-T tilting MRI unit (G-Scanner, ESAOTE, Genova, Italy) is used. The MRI scan includes conventional sagittal T2-weighted (T2w) and T1-weighted (T1w) turbo –spin echo (TSE) sequence and an axial and coronal TSE-T2w sequence covering all lumbar spine segments. In addition, prior to the conventional scanning, all participants will be scanned in the standing weight-bearing position, including a sagittal TSE-T2w sequence and axial and coronal TSE-T2w sequences. Due to the small dimension of the scanner and risk of orthostatic syncope, it may be necessary to convert to conventional supine high-field MRI. This assisting MRI scanning is evaluated for red flag conditions and potential exclusion criteria within 2 weeks, while the scientific semi-quantitative evaluation is performed in detail later. Radiologists from the Department of Radiology, Frederiksberg Hospital, will read all scans, and the physician from The Parker Institute Department of Rheumatology will inform the participants of the MRI findings by telephone or by an informative letter mailed to the patients. The final MRI report will also be sent to the participant’s GP. The participants may be excluded if necessary according to the exclusion criteria after the MRI. Omission on the request of the participant of the follow-up scans will not have an effect on participation in the study.

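### Discretionary exclusion after a post-randomisation MRI does not fit the intention-to-treat population of 300, and the protocol does not say whether excluded participants stay in follow-up and analysis

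*Protocol article*

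**What the plan says.** In the protocol article, Study timeline sets the order of events. After the questionnaires and clinical examination, "the randomisation takes place and the group allocations are revealed to the participants", and the intervention arm has its first session on that same day. For logistical reasons "the participants will be scanned at baseline as a post-allocation examination within 2 weeks". The scan is read for red flags and possible exclusion criteria, and then: "The participants may be excluded if necessary according to the exclusion criteria after the MRI". The MRI report also goes to the participant's GP.

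The Exclusion criteria section lists serious disease, cancer, severe co-morbidity and MRI contraindications. It also lists treatment by, or referral to, outside providers, with surgery as the example. Study settings and recruitment says that GPs are kept informed of the allocation.

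Three statements elsewhere describe who is to be followed and analysed:

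- Sample size bases its final power figure on "Including 300 participants in the intention-to-treat population".
- Statistics says that in the main analysis of 6-month sick leave "participants will be analysed according to the allocated group".
- Statistics also says that the trial will try to follow everyone randomised, including those who stop their assigned treatment.

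**The concern.** An eligibility check that ends after randomisation lets the analysis set depend on what happens after allocation. Late removal does little harm when it concerns a condition already present at randomisation, judged blind and in the same way in both arms. The article secures none of these three conditions:

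- The decision is optional in its wording, so two similar participants could be treated differently.
- The Blinding section covers the assessing physicians, chiefly by asking participants not to mention their arm at follow-up visits. It does not cover the decision to exclude after the MRI.
- The criterion on outside treatment or referral need not be a pre-randomisation condition. The scan report goes to a GP who knows the allocation, and a referral prompted by that report could then meet the criterion.

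At stake is whether the comparison of accumulated sick leave rests on all those randomised. If those excluded have unusual sick leave and the exclusions differ between arms, the estimated difference moves. The direction depends on which arm loses more of them.

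**Working it through.** **1. The plan's own figures.** Sample size gives a "two-sided significance level of 0.05", "assuming a common standard deviation of 17 days", a 6-day difference and a two-sample pooled *t*-test. The noncentrality is δ / (σ√(2/n)).

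- n = 127 per group: 6 / (17 × √(2/127)) = 2.81, exact power 80.0%. The stated 127 reproduces.
- n = 150 per group: 6 / (17 × √(2/150)) = 3.06, exact power 86.1%. The stated 86.1% reproduces.

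The sample-size arithmetic is correct. The 86.1% requires all 300 enrolled participants to be in the analysis.

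**2. The passages side by side.**

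| Step | Place in the article | Timing |
|---|---|---|
| Randomisation, allocation disclosed | Study timeline | Baseline visit |
| First intervention session | Study timeline | Same day |
| MRI and reading for exclusion criteria | Study timeline | After allocation, within 2 weeks |
| Possible exclusion | Study timeline | After the MRI |
| Analysis population | Sample size | All 300 enrolled |
| Follow-up | Statistics | All randomised, as far as possible |

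Nothing in the article says whether a participant excluded at the fourth step still belongs to the last two rows.

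**3. Possible shift in the difference.** Suppose a share q of one arm is excluded, with a mean D days above that arm's full mean μ. The retained mean is [μ − q(μ + D)] / (1 − q) = μ − qD / (1 − q). With no exclusions in the other arm, the difference shifts by qD / (1 − q). The article gives neither q nor D. I assume q = 2% or 3% (3 or 4.5 of 150) and D = 17 or 34 days (one or two of the stated SDs).

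| q | D (days) | Shift (days) | Share of 6 days |
|---|---|---|---|
| 0.02 | 17 | 0.34 / 0.98 = 0.35 | 6% |
| 0.03 | 17 | 0.51 / 0.97 = 0.53 | 9% |
| 0.02 | 34 | 0.68 / 0.98 = 0.69 | 12% |
| 0.03 | 34 | 1.02 / 0.97 = 1.05 | 18% |

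If both arms lose the same share with the same excess, the two shifts cancel and the result is zero.

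**4. Power.** Assume 5% excluded and nothing else lost: 150 × 0.95 = 142.5, taken as 142 per group. Exact power is 84.2%, against 86.1% with everyone retained.

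**The case against.** The strongest reply is that exclusion may mean only that the intervention stops. Statistics says that the trial will try to follow all randomised participants, even those who leave their assigned treatment, and will analyse them by allocated group. On that reading the passages agree, and exact analysis sets are often defined in a fuller document. This reply stands in part. A reader might infer that the protocol flatly contradicts intention to treat. The text does not support that, because it never says that excluded participants leave the analysis. But the follow-up sentence concerns withdrawal from treatment, whereas Study timeline speaks of exclusion under the eligibility criteria, which ordinarily means leaving the trial. The tension is unresolved.

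Second, differential exclusion is not shown. All participants are scanned under one protocol, radiologists from another department read the scans, and the assessing physicians take no part in the intervention. Eligibility is also screened by telephone and at the baseline examination, so most MRI findings leading to exclusion would probably have been present at randomisation. This is fair. A reader might infer that the rule removes those with the longest sick leave, or removes more from one arm. No passage shows either.

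Third, larger shifts can be produced only by assuming a larger excess. An excess of 48 days, for example, is 48 / 17 = 2.8 SDs and has no source in the article.

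Fourth, a reader might blame the MRI rule for power falling below 80%. Drop-out of 20%, the upper limit of what the article expects, leaves 120 per group and 77.7% on its own. Adding 5% MRI exclusion gives 150 × 0.95 × 0.80 = 114 per group and 75.6%. The MRI rule accounts for about 2 points of that fall.

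**Conclusion.** The point holds as an unresolved tension that affects who is in the primary comparison. The article permits discretionary exclusion after allocation is known and treatment has begun, without stating that the decision is blind. It does not reconcile this with a 300-participant intention-to-treat population or with follow-up of all those randomised.

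Bias is possible, not certain, and its direction is unknown. Under one-sided exclusion of 2-3% and an excess of 17 to 34 days, all assumed, the shift is about 0.35 to 1.05 days, or 6-18% of the target difference. It is zero under equal rates and equal excess. The stated sample size and power are correct, and the loss of power from MRI exclusion alone is minor. The case for change rests on protecting the randomised comparison and on not leaving the analysis set open until outcomes are visible.

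**What to change.** Reconcile Study timeline with Sample size and Statistics by adding one statement to the protocol and analysis plan. Every randomised participant stays in follow-up (weekly sick-leave diary, DREAM register, 6-month visit) and in the primary intention-to-treat analysis whatever the MRI shows, unless consent is withdrawn.

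Use MRI-defined ineligibility only in a sensitivity analysis. Judge it blind to allocation and only on conditions present before randomisation, and report the number of such participants by arm.

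The cost is that statement, continued follow-up of those affected, and slight dilution of the effect from a few ineligible participants. The sample size does not change, and the stated 86.1% continues to refer to all 300. The change concerns follow-up and analysis only and does not affect clinical care after an MRI finding. Recruitment was still under way when the article was submitted, so the change could have been made at that stage.
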